#### STUDY ASSESSMENTS - AFTER 30 HOURS OF SULFASALAZINE TREATMENT

- Insertion of a dedicated intravenous cannula
- Six blood ( $\geq 5$  ml collected in pink-topped plasma EDTA tubes each time) tests over one 12 hour period (via the cannula)
- 3 x MSU samples ( $\geq 5$  ml per sample, collected in yellow-topped sterile specimen pots) over one 12 hour period
- At MHW only – Repeated brachial artery flow-mediated dilatation measurements

After these specific samples and measurements are collected, study assessments will follow the pattern of normal clinical care as per local SOP for the treatment of preeclampsia. Study-specific blood samples ( $\geq 5$  ml collected in pink-topped plasma EDTA tubes) to assess for maternal serum biomarkers of preeclampsia will be collected along with any clinically indicated blood tests, as dictated by the treating obstetric team (usually every 2-3 days).

#### STUDY ASSESSMENTS – POSTNATAL

- Collection of 1 x pink-topped plasma EDTA tube (maternal blood) at delivery
- Collection of 1 x pink-topped plasma EDTA tube (cord blood)
- Collection of 6 x 30g placental samples
- Postnatal closing out visit/phone call
- Maternal and neonatal history reviews

Other information required for study assessments (such as blood test results, growth and wellbeing ultrasounds, etc.) that form a normal part of clinical care will be transcribed into the CRF from patient files.

Clinical management may vary slightly between the two participating sites or between the different obstetric units therein. A member of the research team will visit each participant every 1-3 days (or more frequently, as requested by the direct clinical care team), communicate with their clinical carers and review the participant's medical history. The researcher will update the CRF detailing:

- Any AEs experienced by the participant
- Any changes in severity of the signs or symptoms of the preeclampsia disease process
- Any pathology tests undertaken since the last study visit
- Compliance with treatment regime
- Participant wellbeing
- The participant's stated willingness to continue with the study

#### **7.1 SAFETY ASSESSMENTS**

- Trial participants will have baseline observations performed prior to the administration of the 1st dose of sulfasalazine, and will have their wellbeing reassessed by a study Investigator within 3 hours of taking the 1st dose.
- Trial participants will be monitored for serum levels of sulfasalazine as part of the pharmacokinetic component of the trial. These levels are thought to be directly related to incidences of sulfasalazine-induced hypersensitivity reactions and toxicity (see *Section 6.5* and *Appendix 1*).

- As a part of the routine management for women with preterm preeclampsia, participants will undergo frequent, multimodal monitoring of their own condition, as well as that of their baby. This management and these results will be overseen by the participants' treating clinicians, with additional reviews performed by the research team during the collation of results into the CRF.
- All participants will be public hospital inpatients for at least the initial phase of their study involvement, with 24 hour midwifery, obstetric and critical care staff available in case of a serious medical event
- Following delivery of their baby and the cessation of the sulfasalazine therapy, each participant will undergo routine monitoring and follow-up of their preeclampsia to ensure its timely resolution

Following any AE involving a participant, an obstetrician who is also a member of the research team will review the patient and the history of the AE to establish severity and causality of the event (see *Section 10*), determining whether or not the event was likely attributed to sulfasalazine. They will also arrange for any necessary follow up with the patient in an attempt to ensure that the AE is resolved satisfactorily.

## 7.2 SUMMARY TABLE OF STUDY ASSESSMENTS

TABLE 2: Summary of study assessments

|                                         | Prior to treatment commencement | 1 st day of treatment | After 30 hours of treatment | Each subsequent review | Day of delivery (or next weekday) | Closing out visit/phone call |
|-----------------------------------------|---------------------------------|----------------------------------|-----------------------------|------------------------|-----------------------------------|------------------------------|
| Consent                                 | ✓                               | ✓*                               | ✓*                          | ✓*                     | ✓*                                | ✓*                           |
| Medical history review                  | ✓                               | ✓                                | ✓                           | ✓                      | ✓                                 | ✓                            |
| Check results: Clinical pathology tests | ✓                               | ✓                                | ✓                           | ✓                      | ✓                                 | ✓                            |
| Flow-mediated dilatation (MHW)          | ✓                               |                                  | ✓                           |                        |                                   |                              |
| Sulfasalazine levels                    |                                 |                                  | ✓**                         |                        | ✓***                              |                              |
| Biomarkers of PE                        | ✓                               | ✓                                | ✓                           | ✓                      | ✓                                 |                              |
| Adverse events                          |                                 | ✓                                | ✓                           | ✓                      | ✓                                 | ✓                            |

|                                |  |   |   |   |   |   |
|--------------------------------|--|---|---|---|---|---|
|                                |  |   |   |   |   |   |
| IMP regime compliance   |  | ✓ | ✓ | ✓ | ✓ |   |
| Neonatal history review |  |   |   |   | ✓ | ✓ |

\* = Verbally confirm ongoing consent

\*\* = Maternal serum/urine levels taken following 30 hours of sulfasalazine therapy

\*\*\* = Maternal blood, placental and cord blood levels

### 7.3 LONG TERM FOLLOW UP ASSESSMENTS

At the time of application, there are no plans for long term follow up of the study cohort.

### 7.4 STORAGE AND ANALYSIS OF SAMPLES

The research team will organise for the collection, transport, short-term storage, processing, analysis and disposal of the following blood, urine and placental samples:

- 6 x blood samples collected during one 12 hour period  $\geq 30$  hours following the 1st dose of sulfasalazine to assess for maternal plasma levels and pharmacokinetic activity of sulfasalazine
- 3 x MSU samples collected during one 12 hour period following the commencement of sulfasalazine therapy dose to assess for maternal excretion of sulfasalazine and its metabolites
- Subsequent study blood samples collected concurrently with routine pathology to assess for maternal serum biomarkers of preeclampsia
- Maternal blood, cord blood and placental samples collected at delivery

Research samples for this study will be managed at the University of Melbourne Department of Obstetrics and Gynaecology laboratory at the Mercy Hospital for Women and the research laboratory at Sunshine Hospital. These samples will be handled and analysed by appropriately qualified members of the research team and laboratory staff in accordance with University of Melbourne laboratory SOPs. These samples will be disposed of as soon as they are processed and the required data has been extracted.

All other pathology samples will be sent for analysis to each participating site's contracted pathology provider. The research team will only access the results of these tests from patient files to be

transposed into the CRF. Responsibility for the ordering, collection, transport, analysis, storage, and disposal of these samples will remain with the clinical care team and the local pathology service providers (as appropriate).

## **8 DATA COLLECTION**

The participants' medical records and pathology results are considered to be source data. Information will be transcribed or copied (with abridgments, where appropriate) into the CRF. Data will be collected and transcribed as it becomes available, at each point of contact that the research team has with the participant. It is anticipated that with a small sample size and multiple Co-Investigators/Associate Researchers, participant follow-up will be well-attended and missing data will be kept to a minimum. Where possible, data will be collected from patients regardless of their compliance with the treatment regime (see *Section 9.2.3*). Study protocol compliance will be commented on in the study analysis. The researchers will attempt to collect and report on reasons for any missing data or deviations from study medication regime.

## **9 STATISTICS AND DATA ANALYSIS**

### **9.1 SAMPLE SIZE CALCULATION/RATIONALE**

The researchers plan to recruit 20 women with preterm preeclampsia over a period of 2 years. The researchers believe that this sample size is justified as follows:

- Many 'first in man' studies will recruit 10 to 20 participants. Whilst sulfasalazine is already given to pregnant women for other treatment indications, it has not yet been administered to an exclusively preeclamptic cohort
- 20 is a modest number, however it will be sufficient to obtain pharmacokinetic information and give preliminary data about sulfasalazine's capacity to have a clinical or biochemical effect on the disease mechanisms of preeclampsia
- A recent case report published in the American Journal of Obstetrics and Gynaecology (18) examined the effect of pravastatin in a sample size of 20 pregnant patients. This study primarily assessed the pharmacokinetics of pravastatin in pregnancy and also observed the incidence of preeclampsia
- The researchers are targeting preterm preeclampsia, which is a rarer occurrence than term preeclampsia. 20 participants is a realistic number that can be recruited over 2 years, when accounting for those cases that will inevitably decline inclusion or will be otherwise excluded from participating.

### **9.2 PROPOSED ANALYSES**

Statistical analysis for this study will be performed using *GraphPad Prism 6* (GraphPad Software, La Jolla, CA). Given the study design and objectives of this particular trial:

- There is no comparison arm, so clinical variables and the clinical course will be presented as descriptive statistics
- There is no power calculation to perform
- Maternal and neonatal continuous variables will be statistically analysed using a t-test (parametric) or a Mann-Whitney test (non-parametric), as appropriate
- Categorical variables will be statistically analysed using a chi-squared test or Fisher's exact test, as appropriate
- Biomarker concentrations will be assessed as continuous variables
- Steady state sulfasalazine pharmacokinetic parameters will be estimated using standard non-compartmental techniques and normalized using actual body weights
- A p value of <0.05 will be considered statistically significant.

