#### Clinical endpoints/measures of interest:

- Adverse Events (AEs) in mother and/or baby
- Time (days) to delivery of pregnancy after initial sulfasalazine dose
- Change in maternal systolic and diastolic blood pressure (mmHg)
- Change in maternal proteinuria (g/mmol)
- Emergence of/change in other clinical symptoms of preeclampsia
- Maternal development of Haemolysis/Elevated Liver enzymes/Low Platelets (HELLP) syndrome
- Neonatal morbidity/mortality outcomes
- Acceptability of treatment and side effects to participants

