## **3 STUDY DESIGN**

This study is an early (phase II), unblinded, single-arm, proof of concept clinical intervention trial aiming to assess the safety and pharmacokinetic profile of sulfasalazine as a treatment for preterm preeclampsia.

20 participants with singleton pregnancies between 30+0 and 36+0 weeks gestation will be recruited over a two year period. Recruitment will occur at the Mercy Hospital for Women (15 participants) and Sunshine Hospital (5 participants) following a patient's antenatal admission to hospital with a diagnosis of proteinuric preeclampsia, as per the Society for the Study of Hypertension in pregnancy guidelines(1).

All recruited participants will receive 3 grams of sulfasalazine upon enrolment in the study. The following pathology tests will be collected in relation to the study:

Once the participant has been taking sulfasalazine for >30 hours:

- 6 x blood samples ( $\geq 5$  ml per sample collected in pink-topped plasma EDTA tubes) to assess maternal plasma levels and pharmacokinetics of sulfasalazine will be collected from the patient's dedicated intravenous cannula during one 12 hour period
- 3 x Mid-stream urine (MSU) samples ( $\geq 5$  ml per sample) to assess for maternal sulfasalazine excretion will be collected in one 12 hour period.

During remainder of pregnancy:

- When blood tests are collected as part of clinical care, an additional sample ( $\geq 5$  ml per sample collected in pink-topped plasma EDTA tube) will be collected to assess maternal serum biomarkers of preeclampsia including:
  - Anti-angiogenic factors associated with preeclampsia (sFlt-1 and sENG)
  - Biomarkers of endothelial injury (V-CAM, I-CAM and Endothelin)
  - 10 cytokine bioplex assay

Postnatally:

- Maternal blood (1 x pink-topped plasma EDTA tube), umbilical cord blood (1 x pink-topped plasma EDTA tube) and placental samples (6 x 30 g tissue samples) will be collected at delivery to assess for circulating sulfasalazine levels in both mother and baby

The hospitals' local Standard Operating Procedures (SOP) of managing preterm preeclampsia (including blood tests  $\geq 3$  times per week; twice weekly growth and wellbeing ultrasounds; *umbilical artery (UA) Doppler* and CTG monitoring 3 times per week) - or management as otherwise ordered by the treating obstetric unit – will be followed.

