## **5.5 RANDOMISATION**

Not applicable – this is a single arm, unblinded study.

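### Section 9.2 fixes independent-group tests at p<0.05 for a one-arm trial whose effect measures, apart from gestation prolongation, are before/after or serial within the same woman

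*Protocol*

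**What the plan says.** Section 5.5 states that "this is a single arm, unblinded study". Section 9.2 draws the natural consequence: "There is no comparison arm, so clinical variables and the clinical course will be presented as descriptive statistics". The same list then prescribes hypothesis tests. For continuous data it says "Maternal and neonatal continuous variables will be statistically analysed using a t-test (parametric) or a Mann-Whitney test (non-parametric), as appropriate". For categorical data it names chi-squared or Fisher's exact test. It closes with "A p value of <0.05 will be considered statistically significant". It does not say what is compared with what. The Analysis row of the Trial Summary repeats the list.

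The measures of effect are set out elsewhere:

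- Section 2.2.2 lists changes in systolic and diastolic pressure and in proteinuria.
- Section 7 schedules flow-mediated dilatation before the first dose and again after 30 hours, at Mercy Hospital for Women only.
- Sections 7 and 9.2.2 plan biomarker samples through to delivery, taken with clinical bloods, usually every 2-3 days.
- Sections 2.1.2 and 9.2.2 compare gestation prolongation with a contemporaneous cohort. This is the only second group mentioned.

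On the pre-dose biomarker sample the document is split. Table 2 ticks biomarkers before treatment and on day 1, and Section 9.2.2 starts them at recruitment. Section 3 lists these samples after the pharmacokinetic profile, for the remainder of the pregnancy. Section 7 shows no biomarker draw before treatment or on the first-dose day. It introduces them only after the 30-hour samples: "After these specific samples and measurements are collected, study assessments will follow the pattern of normal clinical care". Section 7.4 likewise describes them as later samples.

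**The concern.** Two statements in one list cannot both be followed: either the results are descriptive, or they are tested at 0.05. If they are tested, the tests have to match the comparison. Mann-Whitney, chi-squared and Fisher's exact test assume that the two sets of values come from different people. Here most contrasts set a woman's later value against her own earlier one. No signed-rank, McNemar or repeated-measures method is named. Neonatal outcomes have neither an earlier value nor a stated second group, so a test on them has nothing to compare.

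At stake is the preliminary evidence on clinical and biochemical effect that Section 9.1 offers as part of the case for 20 women. An independent-group test discards the within-woman correlation, which is the main source of precision in so small a one-arm study. If staff follow the text of Sections 3 and 7 rather than Table 2, there is also no pre-dose biomarker value, and no later analysis can recover it.

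**Working it through.** **Is there a figure to reproduce?** No. The protocol gives no power, effect size or SD, and states that there is no power calculation to perform.

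**Inputs from the protocol.** n=20 (Section 9.1); about 15 for flow-mediated dilatation (Section 3, expected recruitment at Mercy Hospital for Women); significance level 0.05 (Section 9.2), taken as two-sided because sidedness is not stated.

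**Assumptions, not in the protocol.** Within-woman correlation rho from 0.3 to 0.7 (0.8 in one example); a shift of 0.5 SD for the power illustrations; normal data with equal variance before and after.

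**Step 1: type I error of an independent-group test on pairs.** The difference in means has variance 2(1-rho)/n in SD units, but the unpaired test uses 2/n. To a normal approximation, the true level is 2P(Z > 1.96/sqrt(1-rho)):

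- rho 0.3: 1.96/0.837 = 2.34, level 0.019
- rho 0.5: 1.96/0.707 = 2.77, level 0.006
- rho 0.7: 1.96/0.548 = 3.58, level 0.0003

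Simulation for Mann-Whitney at n=20 (20,000 runs) gives 0.022, 0.009 and 0.002. The paired t and signed-rank tests stay between 0.044 and 0.052 at these correlations.

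**Step 2: power for a 0.5 SD shift (simulated; signed-rank 3,000 runs).**

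| n | rho | Mann-Whitney | Signed-rank |
|---|---|---|---|
| 20 | 0.3 | 30% | 42% |
| 20 | 0.5 | 27% | 55% |
| 20 | 0.7 | 24% | 76% |
| 15 | 0.3 | 20% | 31% |
| 15 | 0.5 | 18% | 41% |
| 15 | 0.7 | 14% | 61% |

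The signed-rank figure at n=20 and rho 0.5 lies between 53% and 55% across runs.

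**Step 3: flow-mediated dilatation where a paired test is adequate.** At n=15 a paired t-test has 80% power at a mean change of 0.778 SDs of the differences. In SDs of a single measurement this is 0.778 x sqrt(2(1-rho)), which is 0.78, 0.60 and 0.49 for rho 0.5, 0.7 and 0.8. Mann-Whitney at those changes has about 52%, 25% and 12%.

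**Step 4: paired binary data.** With n=20, 2% of women changing one way and 30% the other (assumed), Fisher's exact test has 23% power and exact McNemar 46%.

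**Step 5: one baseline sample against pooled later samples of the same women.** With 3 or 5 later samples and rho 0.3 to 0.7, the type I error of Mann-Whitney is 0.022 down to 0.001, again conservative.

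**Step 6: the cohort comparison.** For 20 women against an independent cohort of 20, 40 or 60, the type I error of Mann-Whitney is 0.047 to 0.050. The named test is of the right type there.

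**The case against.** The strongest reply is that the wording leaves room. A t-test can be paired, nothing says it is not, and the sentence ends by leaving the choice to what is appropriate. A careful analyst could run a paired t-test on normally distributed changes and stay within the protocol. That stands, and it means the power losses above arise only if an independent-group test is chosen. It does not rescue the non-parametric and categorical alternatives, because the tests named have no paired form.

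A second reply also stands in part. Independent-group tests are right for gestation prolongation against the contemporaneous cohort, so they should not be removed altogether. That cohort is mentioned for gestation prolongation only, however, and does not give the other variables a comparator.

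A reader might infer that the plan invites false positive findings, in two ways. The first is that treating serial biomarker samples as independent inflates the type I error. That happens when samples are pooled in a comparison between two groups of women. No second group is planned for biomarkers, and no section says samples will be pooled. For baseline against later samples in the same women the error goes the other way (step 5). The second is that many markers tested at 0.05 make a chance finding likely. That calculation needs independent tests, each at a true 5%. The tests criticised here fall well below 5% on before/after data, and related markers are unlikely to be independent.

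Finally, random-effects structure and similar detail may sit in an analysis plan that is not shown. That is fair for the detail, but the protocol itself fixes the tests.

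**Conclusion.** The point holds in a limited form. Section 9.2 contradicts itself on whether results are descriptive or tested. Its non-parametric and categorical tests do not fit the before/after and serial measures that make up most of the effect data. The error is conservative: p-values would be too large and real changes missed, rather than falsely declared. At n=20 the true level is about 0.02 to 0.002 for correlations of 0.3 to 0.7. At correlation 0.5 and a 0.5 SD shift, Mann-Whitney has roughly half the power of signed-rank (27% against 53% to 55%). Correlation and shift are assumptions. The direction holds for any positive correlation; the size depends on its value.

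The mismatch on the pre-dose biomarker sample is a genuine conflict within the protocol, and it affects whether biomarker change can be computed at all.

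This is a should-fix. The primary objectives, safety and pharmacokinetics, rest on event review and non-compartmental estimation, and do not depend on these tests.

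**What to change.** In Section 9.2, and in the matching row of the Trial Summary, state the comparison for each type of measure:

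- **Before/after continuous measures:** paired t-test or Wilcoxon signed-rank.
- **Paired binary measures:** McNemar's test.
- **Serial biomarkers and laboratory values:** a mixed model with a random effect for woman.
- **Gestation prolongation against the contemporaneous cohort:** keep the independent-group tests, for this comparison only.
- **Single-group maternal and neonatal outcomes:** descriptive summaries with confidence intervals and no tests.
- **P-values:** label all of them exploratory in place of the bare 0.05 rule.

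Reconcile Sections 3, 7 (day of first dose and after 30 hours) and 7.4 with Table 2 and Section 9.2.2, so that the pre-dose biomarker sample is drawn.

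The cost is a short rewording, minor extra analysis work, possibly software other than that named in Section 9.2 for the mixed model, and one extra tube before the first dose.

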If successful, at the completion of this study, we will have sufficient evidence to progress the investigation of sulfasalazine as a treatment for preeclampsia to a large-scale, randomized clinical trial. We hope that it may form the basis for a future medical treatment for preeclampsia and reduce the devastating burden of this common obstetric disease.

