### **1.2 RATIONALE FOR THE STUDY**

## Potential new medical therapeutic option for preeclampsia – sulfasalazine

Sulfasalazine is an anti-inflammatory medication with antioxidant properties that is currently indicated for use in the treatment of inflammatory bowel disease and rheumatoid arthritis. Importantly, sulfasalazine therapy is able to be safely continued throughout a pregnancy (classified as a 'category A' drug) (13). Given sulfasalazine's acceptability as a therapy during pregnancy, coupled with its known anti-inflammatory and anti-oxidant properties, we examined whether it might mitigate key features of the preeclampsia disease process *in vitro*.

We have demonstrated that sulfasalazine reduces sFlt-1 and sENG secretion from human placenta, including from placental samples obtained from patients diagnosed with preterm preeclampsia (Figure 1A). Importantly, we have also shown that it can significantly improve vascular function by quenching markers of endothelial dysfunction (Figure 1B) and induce whole blood vessel dilation.

[figure not shown]

**Figure 1:** Sulfasalazine reduces A) sFlt-1 secretion from preeclamptic placenta and B) a marker of endothelial dysfunction VCAM-1 induced in endothelial cells with the addition of preeclamptic serum.

Given the promising *in vitro* data and sulfasalazine's established safety profile in pregnancy, we now wish to progress this concept to the clinic. We hope to recruit 20 participants with preterm preeclampsia and treat them with 3 g of oral sulfasalazine per day. The primary aims of this study are to:

- Assess the pharmacokinetic profile of sulfasalazine administered to pregnant women with preterm preeclampsia
- Gain further information on the safety profile of sulfasalazine therapy administered to women with preterm preeclampsia

Secondly, we will assess key clinical and biochemical features of preterm preeclampsia in women taking sulfasalazine. If effective, this will provide the first evidence that sulfasalazine may be a treatment for preeclampsia in humans. It will form the basis for a larger randomized controlled clinical trial aiming to establish sulfasalazine as a medical treatment for preeclampsia.

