#### **2.1.2 Secondary objectives**

To determine the effects of sulfasalazine on the clinical outcomes and biochemical markers of preeclampsia disease progression in preterm pregnancies by assessing for:

- Length of gestation prolongation (when compared with a contemporaneous cohort)
- Occurrence of clinical symptoms of preeclampsia
- Biochemical markers of preeclampsia disease; including but not limited to full blood count, Liver Function Tests (LFTs), renal function, proteinuria and haematological parameters
- Serum biomarkers of preeclampsia including but not limited to sFlt-1, sENG, Placental growth factor, endothelin 1, cellular adhesion molecules and cytokines.

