### **2.2.2 Secondary endpoints**

#### Laboratory endpoints/measures of interest:

- Serum biomarkers of preeclampsia (sFlt-1, sENG, placental growth factor, V-CAM, I-CAM and Endothelin; and 10 cytokine bioplex assay) during disease progression
- Biochemical markers of preeclampsia during disease progression

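### Section 9.2 calls any p<0.05 significant across at least 16 secondary serum biomarkers, with no ranking among them, no multiplicity control and no exploratory label, while Section 1.2 leaves 'effective' undefined

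*Protocol*

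**What the plan says.** The Protocol's Section 9.2 provides for t-tests or Mann-Whitney tests on continuous variables and chi-squared or Fisher's exact tests on categorical ones. It says that biomarker concentrations are treated as continuous, and it ends with "A p value of <0.05 will be considered statistically significant". The analysis entry of the Trial Summary has the same rule. Section 15.1 says the data will be analysed as Section 9 sets out. Section 9.2 also states "There is no power calculation to perform".

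The laboratory list in Section 2.2.2 reads "Serum biomarkers of preeclampsia (sFlt-1, sENG, placental growth factor, V-CAM, I-CAM and Endothelin; and 10 cytokine bioplex assay) during disease progression". Section 2.1.2 leaves the list open: "Serum biomarkers of preeclampsia including but not limited to sFlt-1, sENG".

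The protocol does have tiers. Safety and pharmacokinetics are primary (Sections 2.1.1 and 9.2.1); clinical and biochemical effects are secondary (Sections 2.1.2 and 9.2.2). Within the secondary tier nothing is ranked. After describing the assessment of clinical and biochemical features, Section 1.2 says "If effective, this will provide the first evidence that sulfasalazine may be a treatment for preeclampsia in humans". The protocol does not say what result would count as effective.

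**The concern.** A flat per-test threshold over many outcomes makes a chance finding somewhere in the set quite likely. Because no marker is named as deciding, any one of the 16 could be reported as a statistically significant biochemical effect. The markers may also disagree, for instance sFlt-1 moving one way and a single cytokine the other, and the plan does not say which would count.

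What is at stake is how the biomarker results will be read when a larger randomised trial in pregnant women is considered. The threshold is written into the protocol itself, so this is not simply a detail awaiting a statistical analysis plan. A later plan that limited the significance claims would have to depart from Section 9.2.

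**Working it through.** The protocol gives no power, familywise error rate or calculated sample size, so there is no figure of its own to reproduce.

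**Inputs from the protocol**
- Per-test threshold: 0.05 (Section 9.2). Sidedness is not stated.
- Sample size: 20, single arm (Section 9.1: "The researchers plan to recruit 20 women with preterm preeclampsia over a period of 2 years").
- Named biomarkers: sFlt-1, sENG, placental growth factor, V-CAM, I-CAM and endothelin make 6; the cytokine assay adds 10; 6 + 10 = 16 (Section 2.2.2).

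**Assumptions**
- Two-sided tests at 0.05, one per marker.
- One-sample t-test on within-woman change, n = 20.
- No true change in any marker.
- A common correlation between markers of 0, 0.3, 0.5 or 0.8. The protocol gives no correlation, hence the range.

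**Independent markers**
- At least one p<0.05 in either direction: 1 − 0.95^16 = 1 − 0.440 = 0.560.
- At least one p<0.05 in the favourable direction (2.5% per test): 1 − 0.975^16 = 1 − 0.667 = 0.333.
- Expected number of false positives: 16 × 0.05 = 0.8.

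**Correlated markers** (simulated null data, n = 20, t-tests as above)

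| Correlation | At least one p<0.05, either direction | At least one p<0.05, favourable direction only |
|---|---|---|
| 0 | 56% | 33% |
| 0.3 | 48% | 25% |
| 0.5 | 39% | 19% |
| 0.8 | 22% | 11% |

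**Sensitivity to the count.** The biomarker list in Section 3 omits placental growth factor and so gives 15 markers; for independent markers 1 − 0.95^15 = 0.537, hardly different. Blood pressure, routine laboratory measures and flow-mediated dilatation would raise the count. They are left out because Section 9.2 says both that clinical variables will be descriptive and that maternal continuous variables will be tested, so how many of them would be tested is not settled.

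**After the fix.** One pre-named marker tested at 0.05 has a 5% chance of a false positive, or 2.5% in the favourable direction. With Holm's method across all 16, the smallest p value is compared with 0.05/16 = 0.0031 and the familywise rate stays at or below 5%. False-discovery-rate control limits the expected share of false findings among those declared.

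**The case against.** The strongest reply is that this is an early, single-arm, proof-of-concept trial. Safety and pharmacokinetics are primary, the effect data are called preliminary in Section 9.1, and ranking or multiplicity rules are commonly left to a statistical analysis plan. Most of this is true and limits the point. The gap lies within the secondary tier; it is not a missing hierarchy for the whole trial. But the protocol does not stay silent and leave the matter open: it fixes a significance rule, and that rule sits badly with data described as preliminary.

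A reader might infer that an inert drug would probably produce first evidence of benefit. The numbers do not support that. Such evidence would need a favourable result, and for 16 markers that chance is at most about 33%. Even counting both directions, the chance exceeds 50% only when the markers are close to independent.

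A reader might also infer that one significant marker would by itself trigger the next trial. No section says so. The Lay Summary's "If successful, at the completion of this study, we will have sufficient evidence to progress the investigation of sulfasalazine as a treatment" follows a description in which safety and pharmacokinetics come first, and Section 1.2 says only that the drug may be a treatment. The protocol leaves the condition undefined; it does not tie it to p<0.05.

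Two technical objections also stand. The protocol sets a per-test threshold and never claims a 5% familywise rate, so the figures above do not contradict a stated error rate. And preeclampsia progresses, so uncontrolled change under an inert drug need not be zero. With an assumed drift of 0.5 standard deviations, a single t-test at n = 20 is significant about 56% of the time (25% at 0.3 and 92% at 0.8). Naming one marker does not cure that.

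**Conclusion.** The point holds in this form: the protocol applies an unqualified significance label to at least 16 secondary biomarkers, with no ranking among them, no multiplicity control and no exploratory label, and it leaves effectiveness undefined. By chance alone, at least one marker would be labelled significant with probability of about 22% to 56%, and at least one in the favourable direction with probability of about 11% to 33%, depending on correlation. These ranges rest on one two-sided one-sample t-test per marker, 20 women with complete data, no true change and a common correlation from 0 to 0.8. Repeated testing over time or further outcomes would raise them, but the protocol does not fix either. The point should be corrected. It leaves the primary safety and pharmacokinetic aims untouched.

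**What to change.** In Section 9.2 and the Trial Summary, replace the blanket rule. Name one deciding effect marker before the data are analysed, for example within-woman change in sFlt-1, which the rationale puts first and for which the schedule in Section 7.2 already has a pre-treatment sample. Report all other biomarkers and clinical measures as exploratory, with estimates and 95% confidence intervals and no significance label; or, if significance claims are wanted for the biomarkers, apply Holm or false-discovery-rate control across the 16. In Section 1.2, tie the word effective to that definition.

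The cost is wording only, with no new samples or participants. The downside is that fewer isolated markers can be called significant. The change does not deal with drift in an uncontrolled comparison, which needs separate treatment.
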